### Sample size calculation

Based on our preliminary work, the following effect size and resulting sample size were calculated for the primary outcome parameter, EMGchange, during passive stretch of the biceps brachii in patients with elbow flexor spasticity (one-sided, α = 0.05, power (1–β) = 0.8) compared to healthy participants. (Table 1)

**Table 1 pone.0328528.t001:** Sample size calculation based on the primary outcome parameter (EMGchange (%MVIC)); SD = standard deviation.

Parameter	Mean (patient)	SD (patient)	Mean (healthy)	SD (healthy)	Effect Size	Sample Size per group
EMGchange	19.1	21.1	0.04	0.1	0.91	10

The sample size calculation for the pre-/post-surgical comparison is based on our preliminary data. In a group of 7 patients with elbow flexor spasticity who underwent hyperselective neurectomy (HSN) of the elbow flexors as a surgical treatment, we were able to perform objective spasticity testing of the elbow. For the primary outcome parameter, EMGchange, the following effect size and resulting sample size were determined (one-sided, α = 0.05, power (1-β) = 0.8) (Table 2):

**Table 2 pone.0328528.t002:** Sample size calculation for a pre-/post-analysis based on the primary outcome parameter (EMGchange (%MVIC)) in 7 patients with elbow flexor spasticity who underwent hyperselective neurectomy (HSN) of the elbow flexors; SD = standard deviation.

Parameter	Mean preop	SD preop	Mean postop	SD postop	Effect Size	Sample Size
EMGchange (n = 7)	21.7	23.7	7.4	4.2	0.65	16

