### Statistical analysis

To determine the reliability of the proposed instrumented assessment protocol, a total of 20 patients with spasticity will be included. These patients must not have undergone prior surgery distal to the elbow and must not have received botulinum toxin injections within the past 6 months. A preoperative measurement will be conducted twice for each patient within 1 week to assess the repeatability (test-retest reliability) of the proposed assessment. By correlating the outcome parameters of the two measurement time points, the Intraclass Correlation Coefficient (ICC, interval-scaled data) will be calculated. Similarly, the ICC for healthy participants will be calculated based on the two measurements 1 week apart. The inter-rater reliability will be determined for healthy participants and for patients with spasticity using the measurement at the first time point each. For this purpose, all spasticity assessments will be conducted by two trained examiners. The ICC will then be calculated by correlating the outcome parameters. Standard Error of Measurement (SEM) and Minimal Detectable Difference (MDD) will be reported.

The 20 arms of the healthy participants may include both arms from the same individual. However, measurements will be performed on two separate days. We assume that each arm functions independently without influencing the other side and therefore treat all arms as independent samples, regardless of whether data from both arms of a single participant are included.

A validity analysis in the strict sense is not possible for the proposed methodology, as there is currently no non-invasive valid measurement technique for assessing spasticity. Alternatively, in clinical practice, the subjective scales MAS and TS are used with moderate reliability. Accordingly, the correlation of the determined spasticity parameters by the instrumented assessment method with both scales will be calculated. For this, the Spearman rank correlation coefficient (minimum ordinal data) will be used.

The study design concerning pre-/post treatment analysis corresponds to an experimental prospective cohort study. Initially, the normal distribution of the interval-scaled parameters will be confirmed (Kolmogorov-Smirnov test and visual inspection using histograms).

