After analyzing the preoperative and 6 months postoperative measurements from a minimum of 15 patients, a first interim analysis will be conducted using a paired two-sample t-test to determine any significant changes in the defined outcome parameters (EMG LV, EMG HV, EMGchange, extension deficit for wrist flexors (FCR, FCU), and finger flexors (FPL, FDP, and FDS)). If normal distribution is not confirmed, the Wilcoxon test will be applied.

Upon completion of all postoperative measurements, changes in the defined outcome parameters (EMG LV, EMG HV, EMGchange, extension deficit for wrist flexors (FCR, FCU), and finger flexors (FPL, FDP, and FDS)) across the three measurements (preoperative, 6 months postoperative, 1 year postoperative) will be examined using one-way repeated measures ANOVA. If histogram analysis and the Kolmogorov-Smirnov test indicate that the data are not normally distributed, the Friedman test will be used as a non-parametric alternative to ANOVA for comparing the three measurements.

The significance level α is set at 0.05. For significant differences, a post hoc paired t-test will be conducted, with α adjusted for multiple testing using the Bonferroni-Holm correction.

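### The plan switches to the Friedman test when data are non-normal, but the only post hoc test it names is the paired t-test

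*Protocol article*

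**What the plan says.** All of this is in the protocol article, Statistical analysis.

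- **Normality check.** "Initially, the normal distribution of the interval-scaled parameters will be confirmed (Kolmogorov-Smirnov test and visual inspection using histograms").
- **Interim comparison, preoperative against 6 months.** A paired t-test, with a stated fallback: "If normal distribution is not confirmed, the Wilcoxon test will be applied".
- **Final comparison of three visits.** One-way repeated measures ANOVA. The switch is worded "If histogram analysis and the Kolmogorov-Smirnov test indicate that the data are not normally distributed", in which case "the Friedman test will be used as a non-parametric alternative to ANOVA for comparing the three measurements".
- **Post hoc step.** "For significant differences, a post hoc paired t-test will be conducted", with a Bonferroni-Holm adjustment. The sentence does not distinguish the ANOVA branch from the Friedman branch.
- **Level.** "The significance level α is set at 0.05". No sidedness is given here; the pre/post sample size is one-sided.

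The parameters concerned are EMG LV, EMG HV, EMGchange and extension deficit.

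**The concern.** The non-parametric branch stops halfway. An analyst who finds non-normal data runs Friedman. If it is significant, the only post hoc instruction is a paired t-test, the method whose assumption the check has just rejected. At the interim, the same section handles the same situation consistently by moving to Wilcoxon.

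The Friedman test only says that the three visits differ somewhere. The pairwise tests show whether spasticity fell by 6 months and whether the change held at 1 year. Those results carry the surgical-outcome conclusion, and on this branch the text either gives them an inconsistent test or, on a narrower reading, no test. An analyst who then picks one after seeing the data has an avoidable choice.

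**Working it through.** **1. The branches side by side**

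| Step | Judged normal | Judged non-normal |
|---|---|---|
| Interim, two visits | paired t-test | Wilcoxon |
| Final, three visits | repeated measures ANOVA | Friedman |
| Post hoc pairs | paired t-test, Holm | paired t-test, Holm (as written), or nothing |

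Only the last cell is out of line. This part needs no arithmetic.

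**2. The plan's own figure.** Table 2 gives 21.7 (SD 23.7) before and 7.4 (SD 4.2) after surgery, effect size 0.65, n = 16, for a one-sided 5% test with 80% power. The pre/post correlation is not given; I assume 0.5.

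- SD of differences = √(23.7² + 4.2² − 2 × 0.5 × 23.7 × 4.2) = √479.79 = 21.9
- Effect size = (21.7 − 7.4)/21.9 = 14.3/21.9 = 0.653
- Noncentral-t power at n = 16 = 0.801

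So 16 reproduces. With the effect size rounded to 0.65, power at 16 is 0.798 and n becomes 17, which is rounding only.

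**3. What the choice of post hoc test can cost**

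Inputs: the Table 2 means and SDs; n = 15, the stated minimum for the interim, used here as a stand-in for the final number; two-sided tests. Assumptions not in the documents: a bivariate log-normal shape and a log-scale correlation of 0 to 0.6.

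- Log-scale SD = √ln(1 + (SD/mean)²): 0.886 before, 0.528 after
- Log-scale mean = ln(mean) − (log-scale SD)²/2: 2.685 before, 1.862 after
- Three visits give three pairs, so the first Holm step is 0.05/3 = 0.0167

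| Simulated power, n = 15 | Paired t | Wilcoxon |
|---|---|---|
| at 0.05 | about 77–91% | about 84–99% |
| at 0.05/3 | about 49–72% | about 68–96% |

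The range runs from correlation 0 to 0.6. Repeat runs agree to within one or two points. These figures cover all samples from the model, not only those the normality check would flag.

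**4. Type I error.** If surgery has no effect and the two visits are exchangeable, both tests stay within the nominal 5%: 3.9% for the t-test and 4.8% for Wilcoxon. In this model the issue is power, not false positives.

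**5. If the differences are normal.** Wilcoxon's asymptotic relative efficiency is 0.955, a loss of about 5%. At n = 15, with normal differences of the same mean and SD, power is about 65% for t and 63% for Wilcoxon.

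**The case against.** **The sentence may be meant for ANOVA only.** It does not mention Friedman, Wilcoxon is already named a few lines earlier, and a condensed article may have dropped the parallel. This is a fair reading and limits the point to a clarification. It does not remove it: on that reading the Friedman branch has no post hoc test. The article has chosen to fix the post hoc test, and what it fixes does not fit its own branch.

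**The magnitude rests on assumed shapes.** This stands. The power figures are illustrative, and with normal differences the advantage reverses slightly. The mismatch between the branches does not depend on them.

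**Wilcoxon is not free of assumptions.** Also true. As a test of location shift it relies on symmetric differences. With skewed differences recentred to mean zero, n = 15 and nominal 5%, rejection is about 13% for t and 18% for Wilcoxon. Its validity here rests on the null of exchangeable visits, which is the natural null for no surgical effect.

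**Stronger readings that the document does not support**

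- *That the pilot shows skewness.* Tables 1 and 2 give only means and SDs, from elbow flexors, with n = 7 in Table 2. An SD above the mean (21.7/23.7; 19.1/21.1) suggests right skew if values are essentially non-negative, but EMGchange is a difference and can be negative. The planned outcomes concern wrist and finger muscles.
- *That the check can hardly detect skewness.* For gamma or log-normal data with the preoperative mean and SD, Kolmogorov-Smirnov with uncorrected critical values has power of only about 3–8% at n = 15–16. With the Lilliefors correction it is about 52–61%. The article does not say which version is used, and histogram inspection is part of the check.
- *That the check must be dropped or replaced by Shapiro-Wilk.* Statisticians differ on this; it is a preference, not an error in the plan.

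**Conclusion.** The point holds in a limited form. The post hoc sentence does not follow the plan's own non-parametric branch: read literally it contradicts the normality check, and read narrowly it leaves the Friedman branch without pairwise tests. This conclusion comes from the text alone.

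The practical size is a loss of power on that branch. Under the log-normal assumption it is about 7–8 percentage points at 5% (77 to 84; 91 to 99) and about 19–24 points at the first Holm step (49 to 68; 72 to 96). The estimate depends on the assumed shape and correlation, on n = 15, and on elbow pilot data standing in for wrist and finger muscles. Nothing in the document shows that the wrist and finger data will be skewed or that the normality check will fail to notice it. The correction is worth making because it is specific and nearly free.

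**What to change.** Replace the post hoc sentence with wording such as: *After a significant repeated measures ANOVA, post hoc paired t-tests; after a significant Friedman test, post hoc Wilcoxon signed-rank tests; both with Bonferroni-Holm correction.*

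This is one sentence, needs no new data or patients, and matches the fallback already used at the interim. Its statistical cost is the roughly 5% loss of efficiency if the differences are in fact normal, and it arises only on the branch where they were judged not to be.

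Optionally, the authors could state that the normality check for paired tests is applied to the paired differences, since that is where the t-test's assumption lies. The correction above does not depend on it.

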### Significance of the project

The development of an objective method for assessing wrist and finger spasticity will enhance therapeutic decision-making and postoperative evaluation. This approach aims to minimize the need for multiple surgeries and prolonged hospital stays by providing a comprehensive diagnostic and outcome measurement tool. The long-term goal is to establish a multicentric database for continuous evaluation of surgical interventions.

## Discussion

The project aims to develop an instrumented assessment method to differentiate between wrist and finger spasticity. As a secondary goal, a simulation of potential surgical outcomes is planned. If the developed methodology is successfully implemented, patients with upper limb spasticity could be optimally treated with a single surgical intervention that corrects all deformities, within the framework of so-called “single-event-multilevel surgeries.” This approach could spare patients from previous clinical testing through botulinum toxin injections and multiple surgeries with extended hospital stays by providing a clear diagnosis and treatment plan. Additionally, the instrumented outcome measure would serve as a crucial quality control for the surgical therapy.

The long-term goal is to establish a large multicentric database. This will allow for the continued investigation and assessment of individual surgical steps, despite the varying combinations of surgical procedures, and enable an evaluation of their effectiveness over time. It will offer patients a significant improvement in independence and, consequently, quality of life.

### Study limitations

There are some study limitations that have to be addressed and taken into account when interpreting the data. First there is no consensus on how to normalize EMG data in patients with spasticity. MVIC normalization is most commonly performed, although its well-known limitations in patients with reduced voluntary motor control. There exist no SENIAM guidelines for sEMG electrode placement on the forearm. The muscle bellies are very close together and partially overlap, suggesting significant cross-talk. As a result, it is unclear how reliably the sEMG data can be interpreted on the forearm. All electrode and marker placements will be documented with photographs. The recorded sEMG data will be visually inspected and assessed for potential cross-talk. The measurement effort for each individual patient is approximately 1 hour under the study protocol and needs to be minimized for implementation in clinical routine. Due to the low number of eligible patients, the study group will be heterogeneous and include individuals with CP post-stroke, and post-hemorrhagic spasticity. This has to be considered when interpreting data. Concerning the spasticity itself, there are no differences expected between patient groups. When evaluating upper limb function differences in learned and lost (post-stroke, post-hemorrhage) versus never learned (CP) movement patterns to due disturbed volitional motor control must be considered. At least for test-retest reliability in patients the additional effort for a second preoperative measurement might be too high and there might be not enough patients to be included for this special testing. On the other hand, spasticity is highly influenced by daily conditions, environment, emotional state, and temperature – raising the question of whether a test-retest measurement truly assesses the method itself or merely reflects fluctuations in the patient’s condition.

## Conclusion

This study will provide new insights into the efficacy of instrumented assessment tools for spasticity and their potential impact on surgical treatment strategies. The integration of 3D motion analysis, surface EMG, and musculoskeletal modeling represents a significant advancement in spasticity assessment, with the potential to improve patient outcomes and optimize treatment decisions.
